### Control group

2.3

Pupils in the control group of the study will not receive the *If I Were Jack* intervention and will continue with normal RSE practice. We will determine resistance to assignment to the control group by recording refusal to participate or difficulties with retention at follow-up. If we experience difficulties in this regard, we will consider alternative designs for the main trial.

#### Theoretical framework

2.3.1

The theoretical basis of the *If I Were Jack* intervention has been developed from the research team's systematic review of the literature on adolescent men's attitudes and decision-making in relation to an unintended pregnancy (Lohan, Cruise, O‘Halloran, Alderdice, & Hyde, 2010). The review indicated a number of potential influences on young men's attitudes to adolescent pregnancy and pregnancy outcomes including: social class; religiosity; gender identity (some studies found links between traditionally masculine ideals and perceptions that sexual experience validated a masculine identity); attitudes and subjective norms regarding how significant others (such as partners, friends and parents) would expect them to behave in such a situation; and the idealisation of pregnancy and parenthood. This theoretical framework combines with the well-established Theory of Planned Behaviour (Ajzen, 1988, Ajzen and Madden, 1986) and more recent enhancements of the model such as the Integrated Behavioural Model (Montano & Kasprzyk, 2008) and behaviour change frameworks (Cane et al., 2012), all of which underpin the content of the *If I Were Jack* intervention. The Theory of Planned Behaviour (TPB) suggests that behaviour is influenced by intention, which is in turn influenced by a range of psychosocial mechanisms such as attitudes and beliefs, perceived norms and perceptions of personal control over the behaviour. TPB has been supported by extensive research (for a meta-analysis of this research, see (Albarracin, Johnson, Fishbein, & Muellerleile, 2001) while others have extended the model to include knowledge, skills building and anticipated affect (i.e. the prospect of feeling positive or negative emotions after performing a behaviour) (Abraham et al., 2004, Montano and Kasprzyk, 2008, Rivis et al., 2009). It has also been extended to promote an awareness of relevant broader socio-cultural factors (Abraham et al., 2004) which, in the case of the *If I were Jack* intervention, were drawn from our systematic review on adolescent men and unintended pregnancy (Lohan et al., 2010). It is therefore hypothesised that the *If I Were Jack* intervention will have its effect via its impact on knowledge, skills, beliefs about consequences and capabilities, and increased awareness of social influences which will, in turn, have their impact on behaviour via pathways through a young person's intention to avoid sexual risk taking behaviour.

### Outcome measures and assessment instruments

2.4

Key outcomes are the quality of intervention implementation and recruitment and retention of participants. The study will also pilot the feasibility and acceptability to participants of providing demographic data and answering sexual behaviour questions measuring the proposed primary and secondary outcomes for a future, larger phase III trial. Drawing upon the United Kingdom Medical Research Council Guidelines (MRC, 2008), a phase III study is a randomised controlled trial in which the sample size is statistically powered to capture the effectiveness of an intervention.

In a phase III trial, a reduction in unintended adolescent pregnancy rates would be the ideal primary outcome measure. However, the sample size would need to be large in order to detect an important change in this. We will therefore use surrogate measures associated with reductions in unintended pregnancy: abstinence from sex or avoidance of unprotected sex (2 years past baseline). In the feasibility trial, we will pilot the feasibility and acceptability of collecting these data from pupils at five and nine-month follow-up.

Secondary outcomes in a phase III trial would be six-month impacts on knowledge, attitudes, skills and intentions relating to avoiding teenage pregnancy. These short-term impacts are hypothesised to lead to increased intention to avoid teenage pregnancy. In this feasibility trial, we will collect data from pupils using items developed specifically for use in the study as well as items from a number of adapted standardised measures to provide broad estimates of effect sizes and the feasibility and acceptability of the questions. The measures were chosen because the constructs they measure map closely to the theoretical framework underpinning the intervention. As part of the study, we will develop a measure of intentions to avoid unplanned pregnancy. We will investigate the association between intentions at baseline and behaviour (abstinence or avoidance of unprotected sex) at follow-up. While regression analyses would be used in the main trial to model the impact of intentions on behaviour, the feasibility study is not powered to detect statistical differences and we will present descriptive statistics relating to the primary outcomes.

**Knowledge** will be measured with items which replicate or have been adapted from similar items in existing validated sexual knowledge scales [Sexual Knowledge & Attitudes Test for Adolescents (Fullard, Johnston, & Lief, 2005); Mathtech Knowledge Inventory (Kirby, 1984)] and questionnaires used in previous sexual health studies with adolescents (Carswell et al., 2012, Elliott et al., 2010).

**Communication skills** will be assessed using adapted versions of the comfort in communicating with peers and parents about sex and birth control sub-scales of the Mathtech Behaviour Inventory (Kirby, 1984). We have adapted the sex sub-scale so that it refers to comfort communicating about avoiding pregnancy and added a new item which assesses comfort in communicating with professionals about unintended pregnancy and contraception.

**Attitudes towards unintended pregnancy** will be measured using items from a newly developed measure of intention to avoid unintended pregnancy (see below).

**Awareness of stereotypical gender norms** will be assessed using the Male Role Attitudes Scale (Pleck, Sonenstein, & Ku, 1993) and attitude items relating to male/female responsibility for avoiding unintended pregnancy.

**Awareness of peer norms and parental values and beliefs** relating to avoiding unintended pregnancy will be assessed using the peer and parent sub-scales of the Sexual Socialisation Instrument (Lottes & Kuriloff, 1994).

**Beliefs about capabilities in avoiding unintended pregnancy** and communicating about avoiding unintended pregnancy will be measured using an adapted version of the Sexual Self-Efficacy Scale (Rosenthal, Moore, & Flynn, 1991).

A measure of **intention to avoid teenage pregnancy** will be developed as part of the study.

**Avoidance of sexual risk-taking behaviour** (abstinence from sexual intercourse or avoidance of unprotected sex) will be assessed using eight items adapted from previous sexual health surveys (Carswell et al., 2012, Elliott et al., 2010). Incidence of pregnancy will be recorded in order to establish **pregnancy outcomes.**

### Questionnaire development & piloting

2.5

Before data collection we will develop the questionnaire, based on the measures described above, ensuring that it takes no longer than 30 min to complete (the average length of RSE classes in NI).

In June 2014, we will ask 40 Year 11 pupils (aged 14–16 years) in a school that is not taking part in the trial to complete an online version of the questionnaire. We will solicit qualitative comments on items and use statistical analyses to reduce the length and select items relating to key concepts. This piloting will determine whether data generated from the questionnaire is valid and reliable. Content validity has to some degree already been established through discussion and selection of items within the research team. This will be demonstrated further through the participants’ ability to complete the questionnaire in a timely and consistent fashion. We will use Cronbach's alpha to test whether the individual scales contained within the questionnaire possess internal consistency and reliability when used with the target population. A subset of participants will take part in two focus group discussions to identify any procedural difficulties in completing the questionnaire. Discussions will focus on completion times, language, usability and comfort with the subject matter. If participants indicate dissatisfaction with certain aspects of the questionnaire, these will be reviewed by the research team, who may decide to alter or remove the items.

The resulting questionnaire will then be used in the feasibility study. During the feasibility study we will also ask a sample of pupils in the control group to participate in cognitive interviews regarding the acceptability and feasibility of the questions. Using responses from the entire sample, scales will be assessed for validity by means of exploratory principle components analysis and for internal consistency by Cronbach's alpha.

### Sample

2.6

Seven post-primary schools in NI will be recruited to the feasibility trial. Eligible schools will include those that currently have a Year 11 group (i.e. adolescents aged 14–16 years). There are 216 such schools in NI in 2012/13. Schools will be excluded if they are defined as hospital, independent or Irish language schools or have less than 30 pupils in Year 11. The study sample will also be stratified to reflect the main categories of schools. In NI schools are categorised as ‘secondary’ and ‘grammar’ with the latter using academic ability to select pupils. Various management structures exist with ‘controlled’ schools managed by one of five education and library boards and ‘voluntary’ schools managed by a board of trustees (usually local churches). The Catholic Church manages a significant number of voluntary (‘maintained’) schools. Although religion is not a criterion for attendance, most pupils at controlled schools are from Protestant denominations and most of those attending maintained schools are Catholic. There are also a number of ‘integrated’ schools, which aim to provide a religiously mixed environment. In order to capture diversity and reflecting the organisation of education in the special circumstances of NI, recruited schools will consist of the following: 1 controlled integrated; 1 controlled grammar; 2 voluntary Catholic grammar; 2 secondary schools in deprived areas; and 1 voluntary ‘other’ management.

Potentially eligible schools will be identified from those attending RSE teacher training (as provided by the Public Health Agency of NI). This training session will introduce the intervention and provide an overview of the research. RSE teachers in attendance will be asked to indicate if they are interested in receiving more information about the research. The schools that we will approach in the first instance will be selected on the basis of 1) their expressed interest and 2) their fit with our recruitment criteria. Schools which decline to participate will be replaced by the next listed school from the list of all eligible schools stratified by school management type and deprivation.

The target population is adolescents aged 14–16 in Year 11. The total sample size of seven schools is likely to provide access to approximately 630 pupils. This is based on the average size of year 11 groups in schools in 2011/12 (mean = 114; median = 113) (DOE, 2012) and allows for an 80% consent rate (Henderson et al., 2007).

### Randomisation procedures

2.7

Schools will be the unit of randomisation, with four randomly allocated to the intervention group and three to the control group. After baseline data collection, the two sets of pairs (Catholic grammar and deprived secondary) will be randomised as pairs to ensure that one of each type is in the intervention arm. Simple random selection will be used for the remaining three schools to allocate two to the intervention group and one to the control group.

### Data collection

2.8

#### Feasibility trial

2.8.1

All pupils in Year 11 in the seven recruited schools will be invited to participate, with the schools in the intervention group receiving a four-week intervention, which replaces normal RSE practice, and the schools in the control group continuing with normal practice. Participating pupils will be in the study for approximately one year and asked to complete a questionnaire during an RSE lesson at baseline and at five and nine months after implementation. Schools will be encouraged to allow pupils to complete the questionnaire online but, if this is not feasible, will be permitted to use paper questionnaires. A fieldworker will be in attendance during data collection to administer the questionnaire or oversee access to the online survey. Questionnaires and envelopes (or links to the online survey) will be left for absent pupils to complete. Identical procedures will be adhered to at each of the two follow-up surveys.

#### Process evaluation

2.8.2

The qualitative component of the study aims to assess ways in which the intervention is implemented and received in schools, and to collect information on the context of the schools, which might help explain differences in participation and implementation across schools and outcomes among pupils in the intervention and control groups. The objectives of the qualitative component are:•To record experiences of recruiting schools, also paying attention to refusals;•To record schools’ reactions to being assigned to control or intervention arm;•To further test the face validity amongst pupils of the quantitative instruments (pre and post questionnaires) by conducting cognitive interviews on the topic of the questionnaire (control group only);•To inquire into teacher trainers’ views on the training materials for teachers;•To inquire into teachers’ views on the quality of the training session offered on the intervention (either one to one, or in a group session) and how the research team might develop a webinar and Web 2.0 support structures for future training (intervention group);•To record the current policies on, and provision of, RSE in schools and to assess what RSE was delivered in intervention and control groups during the feasibility trial;•To inquire into teachers’ experiences of using the intervention in the classroom and school context as well as with parents (intervention group);•To inquire into pupils’ experiences of participating in the intervention at school and home (intervention group);•To gain further information on implementation fidelity and teachers’, pupils’ and parents/guardians’ reactions through researcher observation.•To inquire into parents’/guardians’ reactions to their children participating in the intervention as well as the advantages and disadvantages of their own participation; and•To inquire into participants’ experiences of taking part in the trial.

These data will be collected through a triangulation of sources including teachers, pupil and parents/guardians and by a number of different methods, including semi-structured interviews (with 7 teachers and ‘Heads of Year’ or school principals), focus group discussions (with pupils in each participating school), and unstructured observations of a sample of RSE lessons (at least one in each participating school) as well as the parent discussion sessions (in each school in intervention group). During the process of recruiting schools, we will record any communication (by telephone in person or in writing) which indicates reasons for the school's reluctance or refusal to become involved in the study.

#### Economic evaluation

2.8.3

The aim of the economic component is to establish whether the data collection forms we design capture resource use efficiently (i.e. collect the main cost drivers without overburdening the staff) and that the staff find them clear and easy to complete. The capture of the intervention costs will be guided by the template recommended by Ritzwoller et al. (Ritzwoller, Sukhanova, Gaglio, & Glasgow, 2009) which discriminates between trial-related costs and intervention costs (such as staff training, staff time input and teaching materials). This will include any capital costs (equipment and space), labour and other consumption costs associated with the development and delivery of the training materials. Where relevant, we will attempt to assess the variation in such costs across study sites.

A micro costing approach will be taken to estimate the costs of delivering the intervention. Where possible, costs will be gathered prospectively to provide a robust estimate of the resource use and costs associated with the delivery of the intervention. *If I Were Jack* researchers will complete timesheets and expense claim forms (including travel) on a regular basis. School staff will also document their contribution prospectively where possible. Project researchers will record other costs (e.g. training materials, venue costs, food and refreshments) in a dedicated costing spread sheet. Resource use data (e.g. staff time and consumables) will be combined with appropriate unit costs, to estimate a mean incremental cost per child to deliver the intervention, and a mean incremental cost per school. Subsequent costs associated with potential behavioural changes will also be assessed (e.g. contraception use).

### Data analysis

2.9

Primary analyses will be on an intention-to-treat basis, using all participants in the groups they were randomised to, regardless of the intervention received.

*Participant flow and recruitment*: Summary statistics on consent, withdrawal and dropout will be collated for both trial groups. For each group, the numbers of clusters and participants randomly assigned, receiving intended intervention, completing the study protocol, and analysed for the outcomes will be presented in a CONSORT flow diagram (Schulz, Altman, & Moher, 2010).

*Baseline data*: Appropriate descriptive summaries of baseline demographic and questionnaire data for pupils and parents from the two study arms will be tabulated. Descriptive summaries will be produced for baseline data at cluster level where appropriate.

*Pupil outcomes (5 and 9 month follow-up):* Questionnaire data from pupils will be analysed using frequencies and descriptive statistics. Differences between the trial groups and broad indicators of effect size will be reported. As this is a feasibility study, it is not powered to detect significant differences and inferential analyses will not be performed. Descriptive statistics will be used to report the proportion (categorical outcomes) or mean scores (continuous outcomes) for the intervention and control groups. Reliability of psychometric instruments will be analysed through recourse to classical reliability theory involving factor analysis and calculation of Cronbach's alpha.

*Effect size estimates:* As noted, this feasibility study will measure surrogate outcomes associated with reductions in unintended pregnancy such as abstinence from sex or avoidance of unprotected sex (categorical variables). Effect sizes will be calculated from the differences in proportions between the intervention and control groups. A number of secondary outcomes are also being investigated (continuous variables). Effect sizes will be calculated from the differences in the mean scores between the intervention and control groups taking into account the standard deviation.

*Implementation feasibility:* Following transcription of all audio-recorded interviews and removal of any identifying characteristics of specific schools and individuals, the data will be analysed thematically based on the six steps proposed by Braun and Clarke (Braun & Clarke, 2006). In summary, this follows well established practice of qualitative analysis of moving from inductively derived codes from the data along with searching for data on pre-defined themes as derived from our topic guides and the literature on pupils’ teachers’ and parents’ perceptions of RSE as well as unintended pregnancy. These inductively and deductively derived codes will be analysed to form overarching themes emerging from each of the participant groups outlined above. We will use qualitative software (NVivo 10) to organise the data, and we will ensure methodological rigour by establishing credibility, transferability, dependability and confirmability using techniques suggested by Lincoln and Guba (Lincoln & Guba, 1985). In addition, following Hyde et al. (Hyde, Howlett, Brady, & Drennan, 2005), specific attention will be given to analysing the group dynamics of the focus groups as part of the overall interpretive process. In schools in the control group, special attention will be given to the specifics of analysing cognitive interviews. Feasibility of research methods will be assessed by observation in intervention schools using structured schedules, and through interviews with school staff and subjected to the same analysis.

*Cost-effectiveness:* As described above, the costs of delivering the intervention and current RSE will be captured to facilitate a cost analysis of the two strategies. The findings from the separate cost and effectiveness analyses in the feasibility study will be used to inform the design of a future economic evaluation. We will also determine the acceptability and feasibility of collecting self-report data on STIs by including questions relating to this in the questionnaire. This will help determine if we can model the cost effectiveness of the intervention in terms of reducing STIs as part of future research.

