## Discussion

3

The need for gender-sensitive interventions to address teenage pregnancy has been highlighted as a global health need by the World Health Organisation (World Health Organisation, 2011, World Health Organisation, 2012) and others (Marsiglio, 2006, Ries and Sonenstein, 2006, Shepherd et al., 2010). We aim to initiate a process of robust scientific evaluation which will ultimately produce generalisable findings especially relating to gender-specific teenage pregnancy interventions. A successful feasibility study (with some further piloting work outside of NI) would underpin the development of a UK-wide trial. If it is acceptable and effective, the intervention has the potential to be rolled out to large numbers of boys and girls attending schools across the UK and to be of benefit to several groups of people.

Strengths of the study include the evidence-based, user-endorsed intervention and implementation protocol, which draw on scientifically supported behaviour change theories and research evidence regarding the optimal content and components of effective RSE programmes, and are enhanced by team expertise and end-user engagement in the development and evaluation process.

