A limitation of the study includes the potential for implementation failure in busy school settings, and this is a key reason for beginning the evaluation with this feasibility trial. We have taken steps to optimise fidelity to implementation protocol, a factor which has been implicated in failure to demonstrate impact in previous UK-based programmes (Elliott et al., 2013, Wight, 2011). For example, in the SHARE study (a large randomised control trial of comprehensive sex education conducted in Scotland), issues arose with fidelity to the implementation protocol relating to time constraints and the low priority given to delivering the overall programme in some schools (Wight, 2011). We therefore believe that one of the strengths of the *If I Were Jack* intervention is that it is shorter than previous UK based programmes and will demand less time of the already busy RSE teacher. Furthermore, we have developed the intervention in close consultation with end users who have indicated that its content, components and implementation processes are acceptable and feasible. The intervention also includes focused one-to-one training for RSE teachers, which emphasises the importance of fidelity to protocol. We believe that these factors will help avoid the possibility that implementation failure will impede the demonstration of efficacy. On the basis of our preliminary research, and by working through a partnership model to develop this study, we believe that we are in a strong position to overcome the problems in implementing RSE in Northern Ireland and have already found the resource to be culturally sensitive and acceptable to statutory stakeholders and schools.

A further limitation includes the potential impact of cluster effects such as recruitment bias in a future phase III trial. If this feasibility trial progresses to a phase III trial, then the sample size would need to be calculated to take into account the clustered nature of the study, i.e. young people attending the same school are likely to share similarities including geography, socioeconomic status and ethnic background. The trial would therefore require a greater sample size than individually randomised trials in order to account for the cluster effect. Additionally, the resulting analysis would be analysed on two levels, the individual level and the cluster (i.e. school) level.

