As noted, the extant literature includes systematic reviews which indicate the characteristics of effective school-based interventions (Kirby et al., 2006, Kirby, 2002) and recent reviews have shown the value of interactive-computer-based interventions (Bailey et al., 2010, Guse et al., 2012, Roberto et al., 2007). *If I were Jack* is a unique combination of the components of effective RSE which has been developed as a new intervention to specifically target teenage men. The study will thus add value to the broad literature on RSE by testing whether this combination of components when applied in a new intervention especially targeting men is acceptable, leading to informed research to test its effectiveness over the longer term in a larger trial. Furthermore, the specific context in which the study will take place greatly increases the possibility of demonstrating effectiveness in such a trial because, essentially, we would be assessing the impact of *If I Were Jack* by comparing intervention and control schools with (naturally occurring) low levels of RSE provision relating to unintended pregnancy. While research elsewhere in the UK reported good quality provision of RSE (Elliott et al., 2013, Henderson et al., 2007, Stephenson et al., 2003), the current provision of RSE in schools in NI is known to be low. For example, a 2010 survey revealed that a third of 11–16 year olds in NI had not learned about sexual matters and relationships during school lessons (NISRA, 2011). Thus, we have an increased chance of detecting positive change by introducing and evaluating the *If I Were Jack* resource in NI, because the contrast between the intervention and control groups will be greater than that reported elsewhere (Elliott et al., 2013, Henderson et al., 2007, Stephenson et al., 2003). Finally, as this is the first trial of an RSE intervention to include Catholic schools, demonstrating acceptability of this RSE intervention in Catholic schools will be an important contribution to RSE research more broadly.

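### Between-arm effect sizes from four and three schools are to be reported, but the ban on inferential analysis leaves them without any interval

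*Protocol article*

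**What the plan says.** Section 2.6 (Sample) plans a small number of clusters: "Seven post-primary schools in NI will be recruited to the feasibility trial". On pupils it says: "The total sample size of seven schools is likely to provide access to approximately 630 pupils". Section 2.7 (Randomisation procedures) makes the school the unit of allocation, "with four randomly allocated to the intervention group and three to the control group". The two Catholic grammar schools and the two deprived-area secondary schools are randomised as pairs. The other three schools are split two to one by simple random selection.

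Section 2.4 collects questionnaire data partly "to provide broad estimates of effect sizes and the feasibility and acceptability of the questions". Section 2.9 (Data analysis) defines the effect sizes as differences in proportions for categorical outcomes and as mean differences that take account of the standard deviation for continuous ones. The same section says of the study: "it is not powered to detect significant differences and inferential analyses will not be performed". The only cluster-level analysis it names is descriptive summaries of baseline data.

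The cost-effectiveness paragraph of section 2.9 says that the feasibility study's cost and effectiveness findings will inform the design of a later economic evaluation. The Discussion says that, for phase III, "the sample size would need to be calculated to take into account the clustered nature of the study".

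**The concern.** A confidence interval is an inferential quantity. A statistical analysis plan that obeyed section 2.9 could therefore not supply one, so this is something the article fixes rather than a detail left for later. The results would show an effect size for each outcome with nothing to indicate its precision. Calling an estimate broad does not tell the reader how broad.

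This matters because the effectiveness results have a stated onward use in the design of an economic evaluation. Seven schools give very little information about a between-arm difference, however many pupils they contain. A bare difference invites more trust than it can bear.

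**Working it through.** **Inputs from the article.** Seven schools, four against three; about 630 pupils; Year 11 groups with mean 114 and median 113; 80% consent; strata of two pairs and one group of three.

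**The article's own figure.** Schools × year-group size × consent: 7 × 113 × 0.80 = 632.8 (median) and 7 × 114 × 0.80 = 638.4 (mean). Both agree with approximately 630. That is 630 / 7 = 90 pupils per school, or about 360 against 270. The article states no power or precision figure that could be reproduced.

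**Assumptions, not in the article.** ICC of 0.01, 0.02 or 0.05; equal schools of 90; no dropout; outcome standard deviation of 1, so that differences are standardised.

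**Step 1: variance of a school mean.** Design effect = 1 + (90 − 1) × ICC = 1.89, 2.78 and 5.45. Variance of a school mean = design effect / 90 = 0.0210, 0.0309 and 0.0606.

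**Step 2: strata ignored.** SE = √[(1/4 + 1/3) × variance of a school mean] = 0.1107, 0.1342 and 0.1880. Degrees of freedom = 7 − 2 = 5, t = 2.571. Half-width = t × SE.

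**Step 3: strata respected.** The weight of a stratum is n₁n₀/(n₁ + n₀): 1/2 for each pair and 2/3 for the group of three, in total 5/3. SE = √[(3/5) × variance of a school mean] = 0.1123, 0.1361 and 0.1906, if the strata explain none of the between-school variance. Degrees of freedom = 7 − 3 − 1 = 3, t = 3.182.

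| Assumed ICC | Half-width, 5 df | Half-width, 3 df |
|---|---|---|
| 0.01 | 0.28 | 0.36 |
| 0.02 | 0.35 | 0.43 |
| 0.05 | 0.48 | 0.61 |

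**Step 4: a proportion.** The article gives no outcome rate. At an assumed 20%, the standard deviation is √(0.20 × 0.80) = 0.40, so the 5 df half-widths are 11.4, 13.8 and 19.3 percentage points. With 3 df they are 14.3, 17.3 and 24.3.

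**Step 5: what seven schools say about the ICC.** With the usual F-based interval for a one-way ICC (5 between-school df, 90 pupils per school), an estimate of 0.02 has a 95% interval of about 0.001 to 0.15. The matching design effects run from about 1.1 to 14.5.

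**The case against.** The best defence is that descriptive reporting is a legitimate choice for a feasibility trial and that the article makes it consistently. Its key outcomes are implementation quality, recruitment and retention, and it presents the effect sizes only as broad indications. That stands as far as significance tests go. It does not justify withholding intervals, which can be given without any test.

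Several stronger readings are tempting, and the article does not support them.

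- *The trial fails to deliver what its phase III sample size needs.* No section promises the phase III ICC or target difference. The Discussion says only that a later calculation must allow for clustering. The trial will supply consent, retention, proportions and standard deviations.
- *The plan excludes an ICC.* It does not mention one. In a condensed article this may be left to fuller documents, and Step 5 shows how imprecise the estimate would be.
- *The plan treats pupils as independent.* A raw difference without a standard error assumes nothing about independence. The article does not propose an interval that ignores clustering.
- *The Northern Ireland effect is optimistic for a UK-wide trial.* The Discussion does expect that "the contrast between the intervention and control groups will be greater than that reported elsewhere", and says that a successful study "would underpin the development of a UK-wide trial". But it makes the second statement subject to further piloting outside Northern Ireland, and it never says that this effect size will be the UK-wide target.

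The objection also bears on the remedy. An interval on 5 df ignores the paired and grouped randomisation, and this has to be reflected or declared.

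**Conclusion.** The concern holds in a limited form. The wording of section 2.9 shuts out intervals together with tests while still reporting between-arm effect sizes from seven schools. On the assumptions above, a standardised difference would carry a 95% half-width of about 0.28 to 0.48 (5 df, strata ignored) or about 0.36 to 0.61 (3 df, strata respected but uninformative). Strata that explain some of the between-school variance would narrow the second range; dropout would generally widen both. The ICCs are assumed, so the ranges illustrate the likely precision and do not predict it.

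This is a weakness in reporting. It does not touch the trial's feasibility outcomes, and it is worth correcting because the correction is cheap.

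**What to change.** In section 2.9, replace the exclusion of inferential analyses with a statement that no significance tests will be done. Then add:

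- Each between-arm difference will be reported with a 95% interval that takes the school as the unit and reflects the randomisation strata (3 df). If the strata are ignored (5 df), the report will say so.
- These effect sizes will not set the target difference of the phase III trial.
- Optionally, an ICC with its interval may be reported descriptively, with a note that seven schools are too few to size phase III without outside data.

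The cost is some analysis wording and a few lines of code. Recruitment and data collection do not change. The drawback is that the intervals will be wide, but that is the information a reader needs.
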